### Sample size {14}

There are no relevant background data available to power this study, which is exploratory and not powered for statistical significance. The sample size of 20 is based upon expected feasible recruitment into a complex experimental medicine protocol, based on prior experience from AuToDeCRA.

### Recruitment {15}

A number of strategies will be implemented to identify potential participants:Identification by usual Rheumatology care teamIdentification via local Rheumatology departmental databases followed by a mailed study invitation letter from their usual care team and PIS. The letter will include a tear off slip and a stamped return envelope to express a wish for no further contact if applicableIdentification via National Institute for Health Research immune-mediated inflammatory diseases BioResource with consent for contact passed on by BioResource teamEthically-approved advertisement via posters and leaflets including study contact details displayed in the Rheumatology out-patient department and via collaboration with relevant charities, patient groups and Clinical Research networksParticipant Identification Centre sites may be utilised to maximise recruitment via the Northern Regional Rheumatology Network, a group of rheumatology centres within the North East of England

## Assignment of interventions: allocation

### Sequence generation {16a}

Eligible participants will be randomly allocated to one of five groups. Randomisation will be computer generated and performed by delegated and trained members of the research team using a 24-h, central, secure, web-based system (Sealed Envelope™).Group 1 will receive 10^5^ TolDC_CitPep_ administered into inguinal lymph node/sGroup 2 will receive 10^7^ TolDC_CitPep_ administered into inguinal lymph node/sGroup 3 will receive 10^7^ TolDC_CitPep_ administered intra-articularly into a kneeGroup 4 will receive 10^7^ TolDC_CitPep_ administered intra-dermally into the thighGroup 5 will receive standard care and no active intervention (control group)

### Concealment mechanism {16b}

Allocation concealment will be ensured by the use of a centralised web-based service for randomisation (Sealed Envelope™).

### Implementation {16c}

Participants will be enrolled and randomised by delegated and trained members of the research team. The allocation sequence will be generated by Sealed Envelope™.

## Assignment of interventions: blinding

### Who will be blinded {17a}

The study is not blinded. Due to the need for those receiving TolDC_CitPep_ to undergo leukapheresis and TolDC_CitPep_ administration procedures via distinct routes, it is not practical to perform a blinded study.

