### Outcomes {12}

#### Primary Endpoint/Outcome

There is currently no agreed biomarker for tolerance induction. Pragmatically, we shall seek evidence of favourable immunomodulation by selecting from a variety of different modalities including:Increase in proportional abundance of regulatory T cells in peripheral blood by high dimensional cytometryInduction or increase in Interleukin-10 production in peripheral blood mononuclear cells (PBMCs) following citrullinated peptide stimulation, using ELISpot or intracellular flow cytometryReduction in interferon gamma production in PBMCs following citrullinated peptide stimulationChange in proliferative response of PBMCs to citrullinated peptide stimulation, combined with phenotypic (surface marker, cytokine production) correlationA reduction in ACPA titre or diversity of ACPA specificitiesChanges in circulating cytokine levels

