### Procedure for unblinding if needed {17b}

The study is unblinded throughout.

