### Plans for collection, laboratory evaluation and storage of biological specimens for genetic or molecular analysis in this trial/future use {33}

NHS laboratory and tissue typing bloods

Participants will provide NHS laboratory blood samples, which will be analysed in local Trust laboratories and then discarded. These will be collected and tested as per Table 2 below.

**Table 2 Tab2:** NHS laboratory blood samples

Blood set	Tests to be performed	Time points collected	Participants
Set 1	• Cyclic Citrullinated Peptide Antibody (Anti-CCP) • Rheumatoid factor (RhF) • Full blood count (FBC) • Erythrocyte sedimentation rate (ESR) • Coagulation Screen (with derived Fibrinogen) • International normalised ratio (INR) • Urea and electrolytes (U + E) • Magnesium (Mg) • Adjusted calcium • Liver function test (LFT) • C-reactive protein (CRP) • Human immunodeficiency virus (HIV) • Hepatitis B + C • Human T cell Leukaemia Virus (HTLV) 1 + 2 • Syphilis • Cytomegalovirus (CMV) • HLA DRB1 tissue type (except where tissue type is already known) • Follicle-stimulating hormone (FSH) *	Screening	All * FSH can be considered to prove post menopausal state in women < 50 years who have been amenorrhoeic for 12 months and would prefer testing to using contraception for the duration of the study on discussion with the investigator
Set 1B	• HIV • Hepatitis B + C • HTLV 1 + 2 • Syphilis • CMV	Secondary screening visit	Those screened > 38 days before scheduled baseline visit
Set 2	• FBC • U&E • LFT • Phosphate • Mg • Adjusted calcium • Group + Save • HIV • Hepatitis B + C • HTLV 1 + 2 • Syphilis	Leukapheresis visit	All, except participants randomised to Group 5 (control group)
Set 3	• FBC • U&E • LFT • CRP • ESR	Baseline, follow-up visits 1, 2 and 3	All
Set 4	• FBC • U&E • LFT • CRP • ESR • RhF • ACPA	Follow-up visit 4	All
Set 5	• FBC • U&E • LFT • CRP • ESR • Any additional test at the discretion of the investigator	Flare visit	Those completing a flare visit

Peripheral blood research biomarkers

Research blood samples will be obtained at baseline and weeks 1, 3 and 6. This will involve the collection at each visit of 108 ml of blood in a combination of EDTA and serum separator tubes. Some of this sample will be studied immediately within the research laboratory and the remainder processed and cryopreserved for analysis following study completion.

Lymph node aspirate samples

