Lymph node aspirate samples will be obtained by an experienced radiologist using direct ultrasound visualisation to aspirate up to 5 lymph nodes using a 23 Gauge needle and 3-ml syringe under tension. Samples will be immediately passed to a member of the study team for processing and cryopreservation for analysis following study completion.

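### The reason given for an unblinded study covers participants and clinic staff only, yet no masking is provided for those who read the judgement-dependent laboratory primary outcomes

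*Protocol article*

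**What the plan says.** All references are to the protocol article.

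- **Who will be blinded {17a}:** "The study is not blinded". The only reason given is "Due to the need for those receiving TolDC_CitPep_ to undergo leukapheresis and TolDC_CitPep_ administration procedures via distinct routes", from which it concludes that "it is not practical to perform a blinded study".
- **Procedure for unblinding if needed {17b}:** "The study is unblinded throughout". Neither section makes an exception for laboratory readers or analysts.
- **Primary Endpoint/Outcome:** "we shall seek evidence of favourable immunomodulation by selecting from a variety of different modalities". The list covers regulatory T cells by cytometry, IL-10 by ELISpot or intracellular flow, interferon gamma, proliferation with phenotyping, ACPA titre or diversity, and circulating cytokines.
- **Explanation for the choice of comparators {6b}:** the standard care arm omits leukapheresis and TolDC administration and is otherwise handled like the active arms.
- **Plans for collection, laboratory evaluation and storage {33}:** for blood, "Some of this sample will be studied immediately within the research laboratory and the remainder processed and cryopreserved for analysis following study completion". For lymph node aspirates, "Samples will be immediately passed to a member of the study team for processing and cryopreservation for analysis following study completion".
- **Statistical methods {20a}:** with four per arm, the team will look for consistent trends within each arm and compare each active arm with control and with the others.

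**The concern.** The article answers a question about who is masked with a statement about the whole study, and supports it with a reason that applies to part of the study. Leukapheresis and the injection are visible to the participant and to clinic and procedure staff. They are not visible in a cytometry file, on an ELISpot plate or in a proliferation readout.

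Several primary measures need human decisions: where a gate is placed, what counts as a positive response, which readings are excluded. If the person deciding knows the arm, and for change from baseline also the visit, those decisions can drift in the hoped-for direction. This is bias, not noise, so more participants would not remove it. At stake are the within-arm trends and between-arm comparisons that serve the primary objective and are meant to inform a future efficacy study.

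**Working it through.** The plan has no figure on this point to reproduce; its sample size is simply 5 arms × 4 = 20, and no power calculation exists. The check is therefore mainly a comparison of sections.

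**1. Does the stated reason reach the laboratory?** {17a} cites leukapheresis and routes of administration. These identify the arm to participants, injectors and clinic staff. Nothing in the reason concerns sample reading. The conclusion is wider than its reason.

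**2. Is the lack of masking stated or merely not mentioned?** It is stated. {17a} and {17b} together declare the whole study unblinded, throughout, without exception.

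**3. Is masked reading feasible?**
- {6b}: sampling is the same in all arms, so the tubes need not reveal the arm.
- {33}: all aspirates and the non-fresh part of the blood wait for "processing and cryopreservation for analysis following study completion" or the equivalent for blood. Frozen material can be recoded before it is read.
- {33}: part of the blood is studied at once. Arm can still be withheld by labelling tubes with the study number alone. Visit is harder to hide when samples are processed on the day.

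**4. Which primary outcomes are exposed?**
- Clearly judgement-dependent: regulatory T cell cytometry, IL-10 by ELISpot or intracellular flow, proliferation with phenotyping.
- Largely instrument-read: ACPA titre and circulating cytokines.
- Assay not specified: interferon gamma.
- Aspirates: part of the primary objective (Table 1) and said in Participant timeline {13} to contribute to the immunological endpoints. No listed primary modality names them, and the one assay named for them, single-cell RNA sequencing, is exploratory. They support feasibility more than they define the exposure.

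**5. Does anything described separate readers from allocation?** Randomisation is done by members of the research team ({16c}), and aspirates pass straight to a study team member ({33}). The only code described is the eCRF study number under Confidentiality {27}, which serves data protection. The article describes no separation, but it does not say that readers receive the allocation either.

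**6. Illustration of the mechanism, on assumptions only.** Suppose there is no true effect, changes from baseline are normal and centred on zero, a trend counts as consistent when all four participants in an arm move the favourable way, and reading shifts each change by *b* standard deviations. Then P(4 of 4) = Φ(b)^4, and for at least one of four active arms, taken as independent, 1 − (1 − Φ(b)^4)^4.

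| b (assumed) | Φ(b) | One arm | At least one of four arms |
|---|---|---|---|
| 0 | 0.500 | 0.0625 | 0.23 |
| 0.25 | 0.599 | 0.128 | 0.42 |
| 0.5 | 0.691 | 0.229 | 0.65 |

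Neither *b* nor the four-of-four rule comes from the document. The table shows only that arms of four leave little protection against a small systematic shift.

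**The case against.** The strongest objection is that these are two short checklist answers in an article that condenses a fuller protocol. Sample labelling, batching and gating normally sit in that protocol or in a laboratory manual. A reader might infer from the article that samples are scored with arm and visit known; no section says so. That part of the objection stands. It does not rescue the wording: a study-wide declaration is a statement, not an omission. If a manual does code samples, {17a} and {17b} are inaccurate and should say so.

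Other limits also stand:

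- A reader might infer that most material is frozen. The blood split is not quantified, and the assays run fresh are not named.
- A reader might treat every primary outcome as reader-dependent. ACPA titre and circulating cytokines largely are not, and tetramer staining is exploratory.
- The study is exploratory, unpowered and without confirmatory testing, so no formal decision hangs on a gate. This lowers the consequence. It does not remove it, because with no formal testing the interpretation rests directly on the readings.
- Detailed batch layouts and masking of the analyst can be left to the laboratory manual or the planned statistical analysis plan.

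**Conclusion.** The point holds in limited form. {17a} and {17b} declare the whole study unblinded on grounds that justify this only for participants and clinic or procedure staff. As written, nobody reading the judgement-dependent primary laboratory outcomes is masked, although coded reading is feasible for the frozen material and, at least for arm, for fresh blood.

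The possible consequence is bias in the immune signals the study seeks, from gating, threshold or exclusion decisions made with allocation known. Its size cannot be estimated from the document, and the illustrative probabilities carry no weight in this conclusion. The conclusion rests on taking the two blinding statements at their word and on the ordinary need for operator judgement in cytometry, ELISpot and proliferation assays. The document does not show that readers are actually given arm or visit, or that any result will be biased. This is an inexpensive correction worth making, not a defect that invalidates the design.

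**What to change.** 1. In {17a} and {17b}, limit the unblinded status to participants and treating or procedure staff.
2. State that laboratory readers work from coded samples that hide the arm, and for frozen samples hide the visit where possible.
3. State that gates, thresholds and exclusions are fixed before the codes are broken.
4. For blood studied fresh, send tubes bearing the study number and no allocation, and acknowledge that the visit cannot always be hidden.
5. If sample coding is already in place elsewhere, say so in {17a} instead.

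The cost is about one paragraph of protocol text, a code list held by the trials unit that already manages the study, relabelling of frozen samples and minor logistics for fresh ones. The sample size stays at 20, and no participant procedure is added.

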### Procedure for unblinding if needed {17b}

The study is unblinded throughout.

## Data collection and management

### Plans for assessment and collection of outcomes {18a}

All assessments will be performed by a qualified healthcare professional delegated to the task.

Demographics, medical history and medication history will be collected at screening.

Clinical assessment will occur at screening, baseline, week 1, 3, 6 and 12 and any flare visit as required, and include discussion of any new or relevant clinical history including medications, physical examination, RA assessment and vital signs. Physical examination may vary in detail depending upon individual clinical history and will be selected to ensure a comprehensive understanding of participant health.

Assessment of the participant’s RA condition will include the following:Participant global assessment of disease activity visual analogue scale (VAS)—score 0–100 mmPhysician global assessment of disease activity VAS—score 0–100 mmPain VAS—score 0–100 mm66/68 Swollen and Tender Joint CountHealth Assessment Questionnaire Disability Index (HAQ-DI) (not required at screening)—score 0–3 rounded to one decimal place

Participant reported acceptability will take place at week 12 via a study-specific participant completed Acceptability Questionnaire consisting of sequential questions with a score to denote acceptability and a free text box where participants are invited to comment on any aspect of their involvement.

Full details of blood and lymph node aspirate sample collection are provided in section ‘Plans for collection, laboratory evaluation and storage of biological specimens for genetic or molecular analysis in this trial/future use {33}’.

The described assessments alongside the biological specimens will enable the collection of outcomes as set out in section ‘Outcomes {12}’.

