#### Secondary Endpoints/Outcomes

Secondary outcome measures for the study are:Change in ACR 20, 50 and 70, DAS-28, and components thereof at weeks 1, 3, 6 and 12 compared to baselineNumber of reported AEs. AEs will be collected at each timepoint (baseline, 1, 3, 6 and 12 weeks) from clinical assessment and routine blood testingParticipant reported acceptability of the TolDC_CitPep_ product and study-related procedures including leukapheresis and mode of administration. Data will be collected at the 12-week visit via the Participant Acceptability questionnaire

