## Statistical methods

### Statistical methods for primary and secondary outcomes {20a}

AuToDeCRA-2 is not powered for formal statistical significance. Nonetheless, a statistical analysis plan will be developed during the study.

The analysis population will include all subjects who have received their allocated intervention. For AE reporting, the analysis population will be all individuals who provide consent, whether or not they subsequently receive TolDC_CitPep_.

Demographic characteristics, medical history and clinical characteristics collected at screening will be summarised descriptively and tabulated. For categorical variables, the frequency and percentage in each group will be reported. For continuous variables the mean, standard deviation and/or median and interquartile range will be reported.

Within each arm (*n* = 4), we will assess whether there are any consistent trends in the parameters being measured, both for primary and secondary outcomes, and we will compare each of the 4 intervention arms against the control group and each other for primary and secondary outcomes.

Summary statistics capturing differences in immune biomarkers (expressed as percentages, stimulation indices, titres, etc.) and clinical outcomes (descriptive and numeric) will be tabulated and presented graphically. Longitudinal analysis will be performed to compare samples following TolDC_CitPep_ administration at baseline. Given the low participant number in each group (4), no formal statistical testing will be performed other than to explore analysis methods, identify prospective transformations of the data, identify key prospective time points and obtain estimates of the variability in both primary and secondary measures to inform the design of a future efficacy study. Estimates of variability will be based on a mixed effects model including participant, route of administration and sampling time point.

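### Recording HAQ-DI to one decimal place makes equal true changes unequal and can flip the HAQ component of ACR 20/50/70 in borderline cases (minor)

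*Protocol article*

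**What the plan says.** In the protocol article, the section on assessment and collection of outcomes {18a} lists the instruments of the RA assessment with their scales. The HAQ-DI entry ends "HAQ-DI) (not required at screening)—score 0–3 rounded to one decimal place". The same section closes by tying the listed assessments to the endpoints: "The described assessments alongside the biological specimens will enable the collection of outcomes as set out in section" Outcomes {12}. There, the first secondary outcome is "Change in ACR 20, 50 and 70, DAS-28, and components thereof at weeks 1, 3, 6 and 12 compared to" baseline.

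Three further places matter for size. Sample size {14} says that "The sample size of 20 is based upon expected feasible recruitment into a complex experimental medicine protocol". Statistical methods {20a} says "Given the low participant number in each group (4), no formal statistical testing will be performed", apart from exploring methods, transformations and time points and estimating variability for a later efficacy study. Data management {19} puts all participant data in the eCRF and has the RA assessments uploaded to the medical notes.

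The article does not say from which precision HAQ change or ACR response is calculated. Nor does it say whether category scores or an unrounded score are kept.

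**The concern.** The rounding is attached to the score itself, not to its display in a table. If HAQ-DI is the mean of eight category scores of 0 to 3 (the usual scoring, assumed here), it moves in steps of 0.125 and has 25 possible values. A grid of 0.1 cannot represent those steps evenly. Two participants with the same true improvement can then receive different recorded improvements for no reason but their starting score, and a percentage improvement close to 20, 50 or 70% can land on the wrong side.

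Three secondary uses are exposed: the HAQ change itself, the HAQ component of ACR response, and the variability estimate for HAQ carried into the next trial. Relative error is largest at low scores. The trial enrols nil-to-moderate disease activity (DAS-28 below 5.1), in which low HAQ-DI values are plausible, although the article gives no HAQ distribution.

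**Working it through.** The plan states no figure on this point that could be reproduced, so the check is a full enumeration.

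**Inputs.** From the article: range 0 to 3, recorded to one decimal; ACR cut-offs 20, 50 and 70%; change from baseline. Assumed: steps of 0.125, and HAQ-DI as one ACR component. The article does not say how ties are rounded (0.25 or 0.75, for example), so both round-half-up and round-half-even were run.

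**Error in one score.** Of the 25 values, 7 are exact to one decimal, 12 are off by 0.025 and 6 are off by 0.05. Mean squared error = (12 × 0.025² + 6 × 0.05²) / 25 = (0.0075 + 0.0150) / 25 = 0.0009, under either tie rule.

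**Equal true changes.**

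| True improvement | Possible pairs | Recorded as (same under both tie rules) |
|---|---|---|
| 0.125 | 24 | 0.1 in 18, 0.2 in 6 |
| 0.25 | 23 | 0.2 in 11, 0.3 in 12 |

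The recorded one-step change is therefore 20% too small (0.1/0.125 = 0.8) or 60% too large (0.2/0.125 = 1.6).

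**Component status.** Percentage improvement = (baseline − follow-up) / baseline, from unrounded and from rounded scores, over all 25 × 24 / 2 = 300 pairs in which follow-up is below baseline. Pairs whose status differs:

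| Cut-off | Half-up | Half-even |
|---|---|---|
| 20% | 6 (2.0%) | 9 (3.0%) |
| 50% | 3 (1.0%) | 3 (1.0%) |
| 70% | 6 (2.0%) | 6 (2.0%) |
| Any | 15 (5%) | 18 (6%) |

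Examples that hold under both tie rules:

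- 0.625 to 0.500: true 0.125/0.625 = 20.0%, recorded 0.6 to 0.5 = 16.7%. Lost at 20%.
- 0.750 to 0.625: true 0.125/0.750 = 16.7%, recorded 0.8 to 0.6 = 25.0%. Gained at 20%.
- 1.500 to 0.750: true 50.0%, recorded 1.5 to 0.8 = 46.7%. Lost at 50%.
- 0.375 to 0.125: true 66.7%, recorded 0.4 to 0.1 = 75.0%. Gained at 70%.

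The first two reverse the order of the participants: the one with the larger true percentage improvement fails and the other passes.

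**Low scores.** With baseline at or below 1.0 there are 8 × 9 / 2 = 36 improving pairs. Five of them (14%) flip at some cut-off under either tie rule, against 5 to 6% over the whole scale.

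**Added variance.** If the two rounding errors are treated as independent, a change carries about 2 × 0.0009 = 0.0018. The article gives no SD for HAQ change. For an assumed SD of 0.3 to 0.6 (variance 0.09 to 0.36), that is 0.0018/0.09 = 2% down to 0.0018/0.36 = 0.5%.

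**After the fix.** With unrounded scores every one-step change is 0.125, every two-step change is 0.25, and no pair changes status.

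**The case against.** The strongest reply is that the article only describes an instrument in a list of assessments. It gives no rule for deriving change or ACR response. Such rules normally stand in the statistical analysis plan, which is to be developed and is not shown, and the article condenses a fuller protocol. This stands in part. A reader might infer that the article orders rounding before the ACR calculation; it does not say so. What remains is that a rounding rule is stated, the listed assessments are said to supply the outcomes, and no unrounded score is mentioned.

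A second reply is that nothing need be lost, because the RA assessments go into the medical notes and study documents are archived for 30 years. That is fair. It makes the problem recoverable, provided the completed questionnaires are among what is kept.

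A third reply concerns size, and it largely stands. It is tempting to conclude that ACR responders will be misclassified. The enumeration covers one component only. On the standard definition (assumed), both joint counts and three of five further measures must improve, and HAQ is one of the five, so a flip matters only when HAQ decides. No misclassification rate for responders follows from these counts. It is also tempting to say that a rounding error of 0.10 would swallow the whole 20% threshold at a baseline of 0.5. It would not: 0.5 is exact to one decimal, so the error in a change from that baseline is at most 0.05, half of the 0.10 threshold.

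Finally, both the 0.125 step and the role of HAQ in ACR response come from outside the document. They are the usual conventions, but every count above depends on the step.

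**Conclusion.** The point holds as a minor one. The article fixes a recording precision that does not fit the scale, given the 0.125 step. If the recorded score is the one analysed, equal true changes are recorded unequally, and the HAQ component can change status close to a cut-off. The counts describe possible pairs, each weighted equally; the share expected among participants is unknown without a HAQ distribution.

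The consequence is limited. The outcome is secondary, no formal comparison or decision rule rests on it, and the primary immune outcomes do not use it. An added variance of roughly 0.5 to 2% is small beside the imprecision of any SD estimated from 4 participants per arm or 20 in all. The lack of formal testing does not dispose of the point entirely, because trends within small arms and variability estimates are the planned outputs, and the distortion is avoidable.

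**What to change.** Remove the one-decimal rounding from the HAQ-DI entry in {18a}. Hold the eight category scores in the eCRF, or the unrounded HAQ-DI to three decimals. State in the analysis plan that HAQ change and the percentage improvement used for ACR 20/50/70 are derived from the unrounded score, and that rounding applies only to display in tables and figures. For participants already assessed, recompute the score from the completed questionnaires where these were kept.

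If the eCRF already holds category scores or an unrounded value, one clarifying sentence is enough. Otherwise the cost is a change of field format and re-entry for at most 20 participants. No extra visit, assessment or participant is needed.
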